### Control group

Consenting participants nested in the postcodes randomised to the control arm will not receive the lifestyles and parenting intervention, but rather will receive usual care (self-directed access to and use of parenting and child health services). The control group will form the basis of a comparator group of participants to better understand unhealthy weight gain in children with similar characteristics to the intervention group. All study participants will be invited to an overall presentation and summary of the research findings at the conclusion of the study.

### Data management

Data generated in this research will comprise three categories:

#### Study administrative data

Data and documents produced in the conduct of the trial. These include: protocol, master copies of Participant Information Statement and consent forms, signed agreements, master randomisation list, screening logs, enrolment logs. Study administrative data will be collected and stored using standard MS Office software.

#### Research data

Data collected and produced during the intervention phase of the study. These data include participant questionnaire results, signed consent forms, height and weight measurements. Research data will be collected using Qualtrics surveys. Data from Qualtrics Surveys will be extracted in [name], CSV or PDF formats depending on the type of data (e.g. questionnaire results as MS Excel or CSV, eConsent forms as PDF). Once exported from Qualtrics, working research data will be stored in a shared cloud storage via CloudStor (AARNet), as Excel, CSV or PDF formats depending on the type of data (e.g. questionnaire results as MS Excel or Stata, eConsent forms as PDF). Research data will be managed using REDCap electronic data capture tools hosted at Western Sydney University [42, 43]. REDCap (Research Electronic Data Capture) is a secure, web-based software platform designed to support data capture for research studies, providing 1) an intuitive interface for validated data capture; 2) audit trails for tracking data manipulation and export procedures; 3) automated export procedures for seamless data downloads to common statistical packages; and 4) procedures for data integration and interoperability with external sources. Participants will be assigned a Participant ID, which will be used on all data collection instruments and then de-identified for data analysis. Data will have an access rights assigned to it accessed only by the authorised research team members. Data will be retained for 15 years after the completion of the research. Confidentiality will be maintained by using the process of data cleaning. Researchers will remove identifiers to create a clean set of data. This clean dataset will not contain information that identifies respondents, such as a name or address (such identifying information will be stored elsewhere, in separate, protected files). Some identifiers will be easily recognised and dealt with. For example, the names of respondents will be replaced with pseudonyms & addresses will be deleted from the file once they are no longer needed. Only researchers will have access to the data that is collected and stored. Participant’s identities will not be identifiable in publications resulting from this investigation. All analyses will use the de-identified dataset. The identified dataset will not be shared with non-study personnel. However, de-identified data may be shared with other researchers in accordance with the National Statement on Ethical Conduct in Human Research (2007). Teamup (Teamup Solutions AG, 2014-2021) will be used to manage field workers.

#### Third party data

Data will be obtained from the Services Australia (Medicare Benefits Scheme (MBS) records and Pharmaceutical Benefits Scheme (PBS) records) and from State/Territory health data custodians (public and private hospital admissions, emergency departments, ambulance services, outpatient records). Health administrative data will stored in secure password-protected folders. Best practice file-naming conventions will be used include eliminating spaces from file names by using underscores or CamelCase, including dates in standard format YYYYMMDD, and using clear, consistent descriptors. All MBS & PBS data will be destroyed at the end of the retention period and will not be used for any future, unspecified purposes other than this specific research.

### Project management

The Study project will be managed by a team of researchers across Western Sydney University, Sydney, and Monash University, Melbourne. Research staff will use several methods to manage the project. The primary method of project management will be the REDCap data capture software to collect and manage participant information from recruitment and baseline testing through to randomisation, intervention and follow-up testing. Bilingual field workers and group facilitators of the intervention modules will be communicated with via email, phone and Zoom. Research team members will have regular communication and meetings to maintain consistency and adequate flow of recruitment processes and other tasks. Scheduling of testing sessions for field workers will be assigned and managed using Teamup software.

### Statistical analysis

Data on socio-demographics, anthropometry, general parenting, feeding-related parenting, child’s health and quality of life, physical activity and consumption of healthy foods, parents’ health knowledge and health and household costs will be collected. Child’s anthropometric measurements will be taken at baseline, at completion of the intervention and 12 months after completion of the intervention. Height and weight of the participating child will be used to calculate the BMIz score (primary outcome measure) [57, 58]. Cost per BMIz saved and incremental cost per quality-adjusted life-year gained will also be calculated (Incremental cost per quality-adjusted life-year gained at baseline, end of intervention and 12 months following intervention). Parents will respond to self-administered questionnaire on family functioning, feeding related parenting, physical activity and consumption of healthy foods of the participating child, parents’ health literacy, and family and household costs. The analysis will follow an intention-to-treat approach and with supplementary per protocol analysis. Research data will be analysed with Stata 16 [59]. The statistical analysis will use a modelling approach that aims to capture the profile of the intervention group compared to the control group and while accounting for potential unobserved differences between the intervention and control groups that (if not accounted for) could bias results. The models will evaluate the impact of the interventions over time by testing for an interaction between time and intervention group. This will be followed by multivariable linear models after adjusting for baseline characteristics and other variables (standard demographic variables such as age, sex, income, education, and SEIFA). Subgroup analysis will be undertaken for within-intervention group differences between English speaking and Non-English-speaking groups. Model assumptions will be checked and appropriate adjustments to the analysis made where necessary. A *p*-value <0.05 will be considered statistically significant. The cost-effectiveness analyses will be conducted to determine incremental cost per quality adjusted life year gained by comparing the direct costs and outcomes of behavioural parenting and lifestyle program over usual care from a health care perspective at completion of the intervention and at 12 months post-intervention. The within-trial analysis will adopt a micro-costing approach to calculate the costs of resources used to implement the intervention, including training, staff and travel costs; family or household costs (resources related to food shopping and activities); and health care resources. One of the aims of the project is to undertake economic evaluation to evaluate the effectiveness of the proposed intervention for parents or carers from disadvantaged backgrounds, in preventing unhealthy weight gain in children aged 5 to 11 years living in the same household. This requires data linkage to Medicare funded services and dispensing of subsidised pharmaceuticals to capture total health care expenditure and out-of-pocket costs (Services Australia RMS1190). All analyses will be adjusted for clustering and all participant data will be de-identified prior to analysis.

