
The primary hypothesis is that improving family functioning among parents or carers of 5 to 11-year-old children from disadvantaged backgrounds will reduce BMIz score immediately following the intervention, and 12-months post-intervention, relative to a control group. The secondary hypotheses (immediately following the intervention and 12-months post-intervention when compared to the control group) include:The percentage of intervention group families functioning poorly and experiencing parenting-related intergenerational conflicts will be decreasedThe percentage of intervention group families eating a family meal together and adopting healthy dietary practices will be increasedAmong parents and their 5 to 11-year-old children, the mean duration of time spent in physical activity will increase, and screen viewing time will decreaseThe percentage of intervention group parents with adequate knowledge regarding healthy lifestyles (healthy food and dietary choices, healthy eating, physical activity, and sedentary behaviours) will increaseThe self-efficacy of these behaviours in children aged 5 to 11 years will be greater in intervention families than the control group following the intervention program

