### Assessment

Children’s anthropometric data (primary outcomes) will be measured at 0, 10 and 60 weeks by bilingual field workers to assess the changes weight gain. Measurements will include the child’s height and weight according to a standardised protocol. All bilingual field workers will receive appropriate training by research staff prior to collecting data from research participants. Each field worker will also receive an equipment kit with a detailed instruction manual, height and weight measurement guide, and other necessary items to collect participant data. Parents or carers (of the parent- or carer-child dyad) will participate in a face-to-face interview with trained bilingual field workers to collect data on family functioning, feeding related parenting, physical activity and consumption of healthy foods of the participating child, parents’ health literacy, and family and household costs (secondary outcomes). The following outcome measures will be collected via face-to-face survey using Qualtrics software (Qualtrics, Provo, UT):Study specific questionnaire to capture socio-demographic dataFamily Functioning using the McMasters Family Assessment Device [44].General Parenting Questionnaire as a composite measure of general parenting behaviours/practices and constructs (sense of competence/efficacy)Feeding related parenting will be measured using the Child Feeding Questionnaire [45].Child's Health-related quality of life will be measured by the Child Health Utility 9D [46–49].Parent-reported participation in sports and other physical activity, measured using 1 item from the NSW Population Survey 2019 [50].Child adherence to physical activity guidelines will be assessed using a composite measure of parent-reported accumulated moderate to vigorous physical activity (MVAP) of at least 60 minutes per day in 2 reference periods (past 7 days and a typical week).Leisure-time sedentary behaviours of children will be assessed using parent-reported time spent in sedentary recreational screen time (i.e. television, seated electronic games and electronic device use other than for schoolwork) in a typical week. It will be a composite measure using 1 item from the Sax Institute Short survey instruments for children’s diet and physical activity, [51] and 1 item from the Youth Risk Behaviour Surveillance System [52].Consumption of healthy foods will be measured by items from the Child Component NSW Population Health Survey 2007-2008, [53] National Health Survey 2017-2018 [54] and Short survey instruments for children’s diet (the Sax Institute for the NSW Ministry of Health) [51].The Strengths and Difficulties Questionnaire [55] will be used to measure socio-emotional problems.Parental health knowledge will be measured using the Lifestyle & General Nutrition Knowledge Questionnaire [56].Participant Evaluation Questionnaire as a composite measure to assess satisfaction with intervention.

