### Sample size determination

A minimum sample size was calculated on the statistical power required to detect a difference in standardized BMIz score of 0.15 (SD:0.8) with 80% power and 5% significance level. Taking into account a 19% dropout at end of the intervention and an 11% dropout at follow-up as established in our pilot study, [17] the required sample size is 800 participants after accounting for clustering (i.e. 800 parent- or carer-child dyads) (400 in intervention and 400 in the control group).

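### The named time-by-group interaction is, in its usual form, a less precise test of the BMIz effect than a baseline-adjusted comparison, and the plan does not say which model is primary

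*Protocol article*

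**What the plan says.** All references are to the protocol article.

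- **Outcome and visits.** The Assessment section says "Children’s anthropometric data (primary outcomes) will be measured at 0, 10 and 60 weeks by bilingual field workers". The Statistical analysis section makes BMIz the primary outcome measure.
- **Hypothesis.** The Background section states that the programme "will reduce BMIz score immediately following the intervention, and 12-months post-intervention, relative to a control group". That is an effect at each of two follow-up visits.
- **Test.** The Statistical analysis section says "The models will evaluate the impact of the interventions over time by testing for an interaction between time and intervention group". The sentence before it gives the aim of the modelling: to allow for unobserved differences between the groups that could otherwise bias the results.
- **Later models.** Multivariable linear models follow, "adjusting for baseline characteristics and other variables (standard demographic variables such as age, sex, income, education, and SEIFA". Baseline BMIz is neither named nor excluded.
- **Target.** The Sample size determination section aims to "detect a difference in standardized BMIz score of 0.15 (SD:0.8) with 80% power and 5% significance level", with 400 dyads per arm and dropout of 19% at the end of the intervention and 11% at follow-up.

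The text gives no correlation between visits and no intracluster correlation (ICC). It does not say whether the interaction model leaves the baseline means free, or which model gives the primary result.

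**The concern.** The one test that the article names for intervention impact can be read in two ways, and neither makes the best use of the baseline measurement.

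- **Week 0 is an outcome time and the group means there are free.** The interaction coefficient for a visit is the arm difference at that visit minus the arm difference at baseline. Baseline is subtracted with weight 1 rather than the regression weight rho. This loses precision and over-corrects a chance baseline difference.
- **Only weeks 10 and 60 are outcome times.** The interaction asks whether the effect differs between the two visits. A benefit of the same size at both would give no interaction, although that is what the hypothesis predicts.

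Only the first reading tests the stated hypothesis, so it is the more natural one. At stake is power for a small target of 0.15 BMIz, using a baseline value that is collected anyway.

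**Working it through.** **Inputs from the protocol article.** Difference 0.15; SD 0.8; 5% significance (taken as two-sided, which is not stated); 400 per arm; dropout 19% and 11%; 92 postcodes.

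**Assumptions.** The two dropout figures compound, so n at week 60 is 400 × 0.81 × 0.89 = 288 per arm. The SD is the same at each visit. Rho runs from 0.5 to 0.9. The ICC is 0 at first, then 0.02 and 0.05.

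**1. The plan's own figure.** For a follow-up comparison that ignores baseline, n per arm = 2 × (1.960 + 0.842)² × 0.8² / 0.15² = 447, or 894 in total before dropout or clustering. The stated 800 does not reproduce from these inputs. The present point does not rest on that.

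**2. Variance factors**, relative to the follow-up comparison:
- follow-up only: 1
- interaction with free baseline means: 2(1 − rho)
- adjusted for baseline: 1 − rho²

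The ratio of the second to the third is 2(1 − rho)/[(1 − rho)(1 + rho)] = 2/(1 + rho), which is never below 1. A generalised least squares calculation for a saturated three-visit model gives the same factors. With the baseline means constrained equal it gives 1 − rho².

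**3. Size at week 60.** SE = 0.8 × √(2 × factor / 288); power = Φ(0.15/SE − 1.96). For rho 0.5, the interaction has SE 0.8 × √(2 × 1.00/288) = 0.0667 and power Φ(0.29) = 61%. The adjusted estimate has SE 0.8 × √(2 × 0.75/288) = 0.0577 and power Φ(0.64) = 74%.

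| rho | variance ratio | SE of interaction larger by | power, interaction | power, adjusted |
|---|---|---|---|---|
| 0.5 | 1.33 | 15.5% | 61% | 74% |
| 0.6 | 1.25 | 11.8% | 71% | 80% |
| 0.7 | 1.18 | 8.5% | 83% | 88% |
| 0.8 | 1.11 | 5.4% | 94.5% | 96% |
| 0.9 | 1.05 | 2.6% | 99.9% | 99.9% |

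Ignoring baseline gives 61% throughout. The interaction equals that at rho 0.5 and beats it above 0.5.

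**4. Clustering.** The mean cluster size at week 60 is 2 × 288/92 = 6.26. Applying one design effect to both analyses (ICC 0.02: 1 + 5.26 × 0.02 = 1.105) gives 57% against 70% at rho 0.5 and 79% against 85% at rho 0.7. This flatters adjustment if the postcode effect is stable over time, because such an effect cancels in change scores. Allowing for that, the gain at rho 0.7 is about 5 points with ICC 0.02 and about 4 with ICC 0.05. At rho 0.8 it is between 1 and 2 points.

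**5. Chance imbalance.** The baseline arm difference has SE 0.8 × √(2/400) = 0.057 before clustering. A difference D shifts the change estimate by (1 − rho) × D in size. With D = 0.10 the shift is 0.05 at rho 0.5 (a third of the target), 0.03 at rho 0.7 and 0.01 at rho 0.9.

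**The case against.** The article does not write the model out, so free baseline means are an inference. An interaction model with the arms constrained to a common baseline mean also fits the quoted sentence, and it is as precise as baseline adjustment. The later models adjust for baseline characteristics. The bracketed list most naturally explains the other variables and is illustrative in any case. A reader might infer that baseline BMIz is left out of the analysis altogether; the text does not support that. Covariate lists are commonly left to an analysis plan, which is not shown here.

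Differencing also has a stated motive. The plan wants to allow for unobserved group differences, and differencing removes any that are stable over time. In a trial that randomises postcodes, the choice between the two methods is therefore partly a judgement of bias against precision. The same motive makes a constrained baseline mean an awkward fit with the plan.

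Most of this stands, and it limits the claim. It does not remove the point: the interaction is the test that the article names, its usual form is the less precise one, and the article does not say whether that test or the later adjusted models give the primary result.

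**Conclusion.** The point holds as a low-cost improvement in precision, not as an error. A reader might go further and call the planned analysis biased; under randomisation it is not. The shift from a chance imbalance is conditional on that imbalance and averages to zero over randomisations.

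The size depends on rho, which the document does not give. With the plan's inputs at week 60 and no clustering, adjusting for baseline BMIz gains about 12 points of power at rho 0.5, 5.5 at 0.7, 2 at 0.8 and none at 0.9. A stable postcode effect makes the gain smaller. If BMIz is highly correlated between visits, little is at stake for the primary outcome. For secondary outcomes the gain is larger where rho is lower, and below 0.5 a difference in change is less precise than ignoring baseline; the document gives no basis for saying which outcomes fall there. The powers also assume two-sided testing, compounding dropout and equal SDs.

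**What to change.** State that the primary estimate is the arm difference in BMIz at each follow-up visit, from a mixed model of the week 10 and week 60 values. Fixed effects: arm, visit, arm-by-visit, baseline BMIz and baseline BMIz-by-visit. Random effects: child and postcode. Make clear that the test of effect is the arm contrast at a visit, not the arm-by-visit term. Name baseline BMIz in the covariate list of the multivariable models. Use the same form for secondary outcomes measured at baseline, each with its own baseline value. Keep the difference in change as a sensitivity analysis, in view of the plan's concern about unobserved group differences.

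The cost is analysis wording only, with no new data, visits or participants. The one downside is that children with a missing baseline value need a simple stated rule, such as single imputation of the baseline covariate.

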## Background

Childhood obesity is a serious public health problem that tracks from early childhood into adulthood [1, 2]. While the prevalence of childhood obesity has plateaued in most high-income countries, [3] it continues to increase among children from disadvantaged and culturally diverse backgrounds [4–6]. Little attention has been given to trialling interventions to reduce unhealthy weight gain among children from disadvantaged and culturally diverse backgrounds, [7, 8] despite data suggesting that even small reductions in body mass index (BMI) are associated with improvements to cardiovascular risk factors in children [9]. This is a significant issue, since children living in areas with the lowest socio-economic status (SES) are at higher risk of being affected by overweight or obesity than those living in higher SES areas [10–12]. A systematic review of 45 studies found that social disadvantage was associated with increased odds of childhood obesity. Specifically, there was an identified inverse association between adiposity in children and SES in 19 studies (42%) [13]. Moreover, the magnitude of associations between SES and adiposity were further analysed in 24 studies, in which 21 of those found a significant inverse SES-adiposity association [13]. The odds ratio for adiposity in lowest SES children, when compared to highest SES children, ranged from 1.3-6.7, with a median odds ratio of 2.04 [13].

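### The only stated subgroup analysis compares language groups inside the intervention arm, so it cannot separate a difference in programme effect from differences that would exist without the programme

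*Protocol article*

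**What the plan says.** The Statistical analysis section of the protocol article contains a single sentence on subgroups: "Subgroup analysis will be undertaken for within-intervention group differences between English speaking and Non-English-speaking groups". It names no outcome and gives no exploratory or descriptive label. Two sentences later the section sets the general threshold, under which a p-"value <0.05 will be considered statistically significant".

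The only interaction in the section concerns the overall effect: the models work by "testing for an interaction between time and intervention group". Language is not part of it. The adjusted models use baseline characteristics and "standard demographic variables such as age, sex, income, education, and SEIFA"; language is not among the examples. The section closes by promising that every analysis will allow for clustering.

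The article plans a usual-care arm and says what it is for. Under Control group it is described as a "comparator group of participants to better understand unhealthy weight gain in children with similar characteristics to the intervention group". No other section adds a comparison of intervention with control by language group.

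**The concern.** Postcodes are randomised, not languages (Randomisation / group allocation). A comparison of language groups within the intervention arm therefore has no randomised basis. It mixes two things: how much more the programme did for one group than for the other, and how the two groups would have differed anyway. One arm cannot separate them. The control arm can, because it shows the untreated language difference.

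The article's own rationale makes an untreated difference plausible. The Background says that obesity has levelled off in most high-income countries, but that "it continues to increase among children from disadvantaged and culturally diverse backgrounds". If weight trajectories differ by cultural background over the 60 weeks of the trial, analysing change or adjusting for baseline BMIz will not remove that difference.

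The trial is aimed at culturally diverse families, and this is the only analysis stated that bears on language. A reader who wants to know whether the programme works as well for non-English-speaking families could see a difference where the effect is the same, or miss one that is real.

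**Working it through.** The plan gives no figure for the subgroup analysis, so there is none to reproduce. The check has an algebraic part and an illustration.

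**What each contrast estimates.** Let D be the difference in programme effect between language groups and g the difference in mean outcome that the groups would show untreated.

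- Within the intervention arm: English minus non-English = D + g.
- Within the control arm: English minus non-English = g.
- Arm-by-language interaction: (D + g) − g = D.

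The planned contrast equals D only if g = 0. If D = −0.15 and g = +0.15, its expected value is 0 and a real difference in effect disappears.

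**Inputs from the protocol article.** Sample size determination gives 400 families per arm, dropout of 19% and 11%, and a target to "detect a difference in standardized BMIz score of 0.15 (SD:0.8) with 80% power and 5% significance level". It does not say whether 0.8 is the SD of the score or of change.

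**Assumptions, not in the document.** The outcome is BMIz; D = 0; g is 0.10, 0.15 or 0.20; the language split is 50:50 or 30:70; the two dropout rates compound; the test is two-sided at 5%; there is no clustering. One scenario uses an SD of change of 0.5, which is also assumed.

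**Children analysed in the intervention arm.** 400 × 0.81 × 0.89 = 288, a loss of about 28%. A 50:50 split gives 144 v 144.

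**Formulas.** Within-arm SE = SD × √(1/n₁ + 1/n₂). P(significant) = Φ(g/SE − 1.96) + Φ(−g/SE − 1.96).

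**Standard errors.**
- SD 0.8, 144 v 144: 0.8 × √(2/144) = 0.094.
- SD 0.5, 144 v 144: 0.5 × √(2/144) = 0.059.

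**Chance that the within-arm test is significant although the programme effect is identical in both groups:**

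| Scenario | g = 0.10 | g = 0.15 | g = 0.20 |
|---|---|---|---|
| SD 0.8, 28% loss, 30:70 | 16% | 31% | 49% |
| SD 0.8, 28% loss, 50:50 (144 v 144) | 19% | 36% | 56% |
| SD 0.8, no loss, 50:50 (200 v 200) | 24% | 47% | 71% |
| SD of change 0.5, 144 v 144 | 40% | 72% | 92% |

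Worked cell: SD 0.8, 144 v 144, g = 0.15 gives 0.15/0.094 = 1.59 and Φ(1.59 − 1.96) = Φ(−0.37) ≈ 0.36.

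For the arm-by-language interaction, g cancels and the figure is 5% in every cell.

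**Precision of the interaction.** It adds the variance of an equal contrast in the control arm, so its SE is √2 ≈ 1.4 times the within-arm SE: 0.094 × 1.414 = 0.133 with SD 0.8, and 0.059 × 1.414 = 0.083 with SD 0.5. With SD 0.8, its power for a 0.15 difference in effect is 26% (no loss, 50:50), 20% (28% loss, 50:50) and 18% (28% loss, 30:70).

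**The case against.** **The purpose and outcome are not stated.** The subgroup sentence names no outcome, and none of the hypotheses concerns language. The programme uses translated materials and bilingual facilitators, satisfaction with it is measured (Assessment), and the Discussion names engagement of diverse groups as a contribution. Satisfaction and attendance exist only in the intervention arm, so for them a within-arm comparison is the only one possible. This stands, and the fix should leave room for it. It does not justify the sentence for BMIz or other outcomes measured in both arms, which the wording does not exclude.

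**A reader might infer that the plan will present the result as effect modification, or base claims of effectiveness on it.** The article says neither. What the text supports is that the comparison cannot distinguish the two explanations; an error follows only if the groups differ naturally and the result is read as a difference in effect.

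**Some confounders are handled.** The preceding sentence adjusts for baseline characteristics and demographic variables, and clustering is covered. It is not explicit that these covariates carry into the subgroup model. If they do, they would reduce measured imbalance but not unmeasured differences in trajectory.

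**The sentence may mean a comparison within each arm.** Separate within-arm tests still do not test whether the effect differs between language groups.

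**The interaction has low power.** True. That is a reason to report it as an exploratory estimate with its interval. A more precise estimate of D + g does not answer the question about D.

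**Conclusion.** The point holds, as a should-fix. The article fixes the language comparison inside one arm, and that comparison cannot tell a difference in intervention effect from a natural difference between language groups. This is a stated choice of comparison, not a detail left to an analysis plan.

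The size depends on quantities the document does not give. For natural gaps of 0.10 to 0.20 BMIz and equal programme effects, the within-arm test is significant 19% to 56% of the time with the protocol's SD and 144 v 144 children. Across the scenarios, the figures run from 16% to 92%. The highest rest on an assumed SD of change of 0.5 and should not be quoted alone. All ignore clustering, and two of the three gaps equal or exceed the 0.15 that the whole trial is designed to detect. They show the direction and possible scale of the problem; they do not predict it.

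A reader might also infer that the trial's main result is compromised. It is not: the primary BMIz comparison, the time-by-group test, the allocation and the data collection are untouched.

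**What to change.** Replace the subgroup sentence with two.

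1. For BMIz and the other outcomes measured in both arms, assess language as a modifier through an arm-by-language (by time) interaction in the cluster-adjusted model. Report the intervention-minus-control difference with 95% CI in each language group, plus the interaction estimate and its CI, labelled exploratory.
2. Keep any comparison of language groups within the intervention arm as descriptive only, for example for satisfaction or attendance.

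This needs no new data, provided language group is recorded in the same way in both arms, and should be settled before results are seen. The cost is precision: an SE about 1.4 times larger than the within-arm contrast, and about 18% to 26% power for a 0.15 difference in effect under SD 0.8 without clustering. A non-significant interaction should therefore not be read as evidence that the effect is the same in both groups.
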